## Data collection and management

### Plans for assessment and collection of outcomes {18a}

#### Data collection

Shoulder function, pain, imaging, and complications were evaluated at 3, 6, and 12 months after surgery and then every 6 months thereafter.

##### Imaging evaluation

The subacromial space was routinely assessed by radiographs of the shoulder. Shoulder osteoarthritis was assessed according to the HAMADA classification, and the degree of muscle atrophy, fat infiltration and healing of the autogenous fascia latas were evaluated by MRI.

##### Pain score

The relief degree of the patient's shoulder pain was assessed by the VAS scale, where 0 was painless and 10 was severe pain.

##### Evaluation of shoulder function

Constant, UCLA and AESE scores were used to evaluate shoulder recovery and patient satisfaction.

#### Oversight and monitoring

Medical records, registration books, and special records for clinical observation, including doctors’ clinical medical records, are all used in this study.

All data and records relating to clinical observations are kept in the investigator or clinical trial medical facility and made directly accessible to the originator of the clinical trial or the person in charge of the competent authority. Make sure 1 copy of each document and data of the participants, and 1 external HD in the cloud disk of Baidu to guarantee data security.

Clinical observation investigators are responsible for preserving the relevant data collected. No one, other than the members of the study group, ethics committees, or medical regulators, will have access to the data collected in this study without good reason.

#### Quality control

To improve test reliability and reduce differences between operators, the following measures should be taken:Outpatient department by Chief Physician [name];Operations were led by [name].Photos and video recordings were taken for each operation.One person is responsible for the evaluation and statistical analysis of the test data.

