### Concealment mechanism {16b}

The random assignment form is usually triplicated. Copies can be enclosed in an opaque envelope, with one copy provided to the patient, one copy to the researcher and one copy to the evaluator. The patient and researchers unseal it before surgery. The allocation scheme is not disclosed to the evaluators collecting outcome data throughout the study. The statistical analysts will also not know whether participants are in the STR or SCR group until the statistical analysis is completed.

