## Assignment of interventions: blinding

### Who will be blinded {17a}

In this study, double blinding was used, in which surgeons were aware of the surgical protocol. Evaluators and patients were blinded, to minimize ascertainment bias.

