### Interim analyses {21b}

The interim analysis was performed when 50% of the randomly assigned patients reached the primary endpoint. The interim analysis was carried out by independent statisticians who were blinded to the allocation of treatment. The statisticians will report to the independent Data and Safety Monitoring Commission. The results of the interim analysis will be discussed with the Steering Committee at a joint meeting. The steering committee decided to proceed with the trial and will report to the Central Ethics Committee.

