## Oversight and monitoring

### Composition of the coordinating centre and trial steering committee {5d}

The study will be performed by the Sports Medicine Center at Southwestern Hospital. There is no other coordinating centre. The trial steering committee consisted of the ethics committee of the First Affiliated Hospital of Army Medical University (No. AKY2022126) and the clinical research team. The research team consists of two principal investigators who oversee the study and are responsible for medical responsibilities, a study coordinator who plans patient visits, and an investigator who is responsible for data management and trial management. The research team meets weekly to assess progress, identify potential test subjects and work out logistical issues. A statistician was involved in the design of the trial and consulted on statistical issues throughout the study. Study leader [name] identified the enrolled patients in the outpatient department. A researcher collected general patient information. To improve the reliability of the test and reduce the differences between operators, the following measures were taken: All the operations were led by [name], and all the operations were photographed and recorded by video. The test data were evaluated and counted by one person.

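### One person is to evaluate outcomes and analyse the data, so the promised masking of the analyst cannot be assured

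*Protocol article*

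**What the plan says.** The staffing rule appears twice in the protocol article. Under Quality control: "One person is responsible for the evaluation and statistical analysis of the test data". Under Composition of the coordinating centre and trial steering committee {5d}: "The test data were evaluated and counted by one person".

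The masking rule for analysts is in Concealment mechanism {16b}: "The statistical analysts will also not know whether participants are in the STR or SCR group until the statistical analysis is completed". The sentence before it deals with a separate group: "The allocation scheme is not disclosed to the evaluators collecting outcome data throughout the study". Who will be blinded {17a} also declares the evaluators masked: "Evaluators and patients were blinded, to minimize ascertainment bias". Procedure for unblinding {17b} adds that they take no part in the operation.

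Concealment mechanism {16b} also describes who receives the assignment form, including "one copy to the researcher and one copy to the evaluator".

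Statisticians are mentioned in two other places. Section {5d} says: "A statistician was involved in the design of the trial and consulted on statistical issues throughout the study". Interim analyses {21b} says: "The interim analysis was carried out by independent statisticians who were blinded to the allocation of treatment".

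**The concern.** The protocol claims a masked analysis but describes a staffing arrangement that may not deliver one. Coding the arms A and B masks an analyst who sees only the coded dataset. It protects much less when the analyst also scored the patients, because anything that revealed a patient's arm during assessment stays with that person at the analysis.

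Masking matters here because the analysis leaves some judgement open. Statistical methods {20a} has normality assessed partly by inspecting graphs, and the result decides between a t test and a Mann-Whitney test for each metric outcome. Queries about odd values and other data decisions also fall to whoever handles the dataset. Masking is the safeguard the protocol offers against such decisions being influenced by knowledge of the arms. With one person in both roles, the scores also get no independent second look before analysis. At stake is whether the published claim of a masked analysis can be supported.

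**Working it through.** No stated figure bears on this point, so the check sets the sections side by side.

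1. **Are the two roles one or two?** Quality control and {5d} give evaluation and analysis (or counting) to one person. Concealment mechanism {16b} speaks of evaluators and of statistical analysts, both in the plural, with a separate sentence on masking for each. The sections describe different arrangements.

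2. **Is that a contradiction in itself?** No. {16b}, {17a} and {17b} all declare evaluators masked. One masked person who both evaluates and analyses would satisfy every sentence. The question is then whether the evaluator can be relied on to be masked.

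3. **Can the evaluator be relied on to be masked?** Three facts in the protocol speak against it.
   - *Assignment form.* {16b} sends a copy to the evaluator. The text names the patient and the researchers as those who open the envelope before surgery, so the evaluator's copy may stay sealed. Even so, the evaluator holds the allocation.
   - *Scar.* Intervention description {11a} gives STR a transverse incision of about 3 cm at the most medial part of the scapular spine. The SCR description contains no such incision. Someone examining the shoulder could see the difference.
   - *Imaging.* In STR the medial end of the graft is fixed at the scapular spine, and in SCR at the superior glenoid. Imaging evaluation (under {18a}) has healing of the graft judged on MRI, so the images carry information on the arm.

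4. **What follows for the analyst?** If the analyst is a different person who receives only coded data, the facts in step 3 do not reach the analysis directly. If the analyst is the evaluator, as Quality control states, they do. The promise in {16b} then depends on evaluator masking that the protocol itself makes doubtful.

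5. **Do the two mentions of statisticians settle it?** No. The statistician in {5d} has a stated role in design and consultation, and the text neither assigns nor rules out running the final analysis. The independent statisticians in {21b} are named for the interim analysis only, so having different people there does not conflict with Quality control.

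**The case against.** The strongest reply is step 2: the evaluator is declared masked three times, so nothing on the face of the text makes the analyst unmasked. This stands, and it means that the sections are not flatly incompatible. A second reply is that evaluation of the test data may mean processing data consistently rather than examining patients, since the sentence sits under an aim of reducing differences between operators. That reading is possible. The text does not say that one person examines or images every patient, and this point does not assume it. The wording nevertheless leaves the roles merged. A third reply is that the weakness lies in evaluator masking, with analyst masking only a consequence. That is fair, and it is why the fix also covers the evaluator's copy of the form.

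Some stronger readings are tempting but not supported:
- A reader might infer that the final analyst will know the arms. No section says so.
- A reader might infer an inflated type I error from an analyst choosing the more favourable of the t and Mann-Whitney tests. A two-sided p value does not change when the arm labels are swapped, so a fully masked analyst could make the same choice, and separating the roles would not remove it. Under {20a} the choice is also tied to a normality check rather than left free.
- A reader might infer that the interim arrangement contradicts Quality control, or that the trial statistician is confined to consultation. The text supports neither.

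**Conclusion.** The point holds in a limited form. Merging evaluation and analysis in one person undermines the analyst masking that Concealment mechanism {16b} promises, because the protocol gives that person several possible routes to the allocation. This is a risk of bias in analysis decisions and an unsupported masking claim. It is not a demonstrated unmasking.

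The size of any bias cannot be computed from the documents, and no error-rate figure should be attached. Sample size, significance level and power are unaffected.

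The conclusion assumes that the person in Quality control does assess outcomes or read images, or at least has access to the evaluator's material. If the phrase means data processing alone, by someone with no view of patients, scans or assignment forms, the problem reduces to unclear wording. The remedy is cheap enough to be worth making in either case.

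**What to change.** - In Quality control, remove the statistical analysis from the single person's duties, and align the matching sentence in {5d}.
- State that the final analysis is run by the statistician already attached to the trial, who takes no part in outcome assessment and works on a locked dataset with arms coded A and B until the analysis is complete. This makes the existing promise in {16b} achievable.
- In {16b}, withhold the assignment-form copy from the evaluator.

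These are wording changes. {5d} already attaches a statistician to the trial, so the small downside is a data hand-over from evaluator to statistician. The fix does not hide the scar or the graft position from the evaluator. It prevents what the evaluator may have learned from passing directly into the analysis.

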#### Adverse event management

Adverse event recordAdverse events: various surgical complications;Serious adverse events: events that require or prolong hospitalization, cause disability, affect the patient’s working ability, endanger the patient’s life cause death, and lead to congenital malformations during the course of the clinical trial.Adverse event report

Management of adverse events: When adverse events occurred, the investigator should treat them actively and according to surgical management principles without terminating the trial or discontinuing the follow-up. For serious adverse events, in addition to active rescue, the experiment should not be terminated, and observation and follow-up should be continued. The investigator should report to the subject leader within 24 h, timely report to the ethics committee, and record the adverse event in the CRF form. All adverse events should be followed up until remission or stabilization. If the patient dies, a new patient can be enrolled.

### Plans to promote participant retention and complete follow-up {18b}

Study follow-up visits are combined with regular visits at the outpatient clinic to minimize patient burden. The primary outcome is set to be evaluated 3 months after the intervention. All questionnaires can be completed on the day of follow-up.

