### Relevant concomitant care permitted or prohibited during the trial {11d}

#### Postoperative rehabilitation

Post-surgery, the patients were placed in a brace in a neutral position with a small abduction pillow to protect the reconstructed area. Full active range of motion of the elbow, wrist, and hand was allowed immediately. The patient wore the sling at all times, except while showering and during formal physical therapy, for the first 6 weeks. After 6 weeks, the patient was instructed to perform closed-chain passive table slides and scapular stabilization exercises. Active range of motion and strengthening exercises were started approximately 3 months post surgery.

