#### Primary outcome

The ASES score and the Constant-Murley shoulder score were obtained during the preoperative stage, as well as at 3 months, 6 months, 12 months and 24 months.

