### Sample size {14}

Sample size calculation for ASES score analysis was performed with an expected standard deviation (SD) of 5.8, a significance level at 5% and power of 0.90 and resulted in 25 participants in each group (50 participants with allowance for 15% drop-out).

In our previous research on postoperative ASES scores of SCR, the score was 87.6 ± 5.8 at the latest follow-up. The best ASES result published by Mihata was 93.1 ± 8.1 (Structural and clinical outcomes after superior capsule reconstruction using an at least 6-mm thick autogenous fascia latas including the intermuscular septum). With a type I error rate of 0.05 (*α* = 0.05, two-tailed) and a power of 90% (*β* = 0.10), the sample size for the study protocol was calculated as 25 patients per group based on the primary outcome indicator by PASS 2021 (Power Analysis and Sample Size, NCSS, LLC, USA). Assuming a 15% drop-out rate, we plan to recruit 58 participants (29 per group) to the study.

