## Statistical methods

### Statistical methods for primary and secondary outcomes {20a}

The statistical software SPSS 25.0 was used for analysis. The normality of metric data, such as ASES scores, Constant scores, VAS scores, shoulder joint mobility, AHD, surgical duration, intraoperative blood loss, and postoperative drainage volume, was assessed using the Shapiro‒Wilk test and graphical analysis. Intergroup differences in metric data conforming to a normal distribution were evaluated using independent samples *t* tests, while nonnormally distributed metric data were assessed using the Mann‒Whitney *U* test. Count variables, such as the occurrence of complications, were evaluated for intergroup differences using the chi-square test. Paired samples *t* test was employed to assess intragroup differences in normally distributed metric data before and after surgery, while nonnormally distributed metric data were represented by median (interquartile range) and assessed using the Wilcoxon rank-sum test. Comparison of ordinal data, such as Hamada classification, Warner classification, Goutallier classification, and Sugaya classification, was conducted using the Wilcoxon rank-sum test. A *p* value less than 0.05 was considered statistically significant.

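### The protocol gives two conflicting definitions of the primary endpoint and sizes the trial on one score at a visit it never fixes

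*Protocol article*

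**What the plan says.** Four places in the protocol article bear on what decides the trial, and a fifth depends on them.

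- **Primary outcome (under Outcomes {12})**: "The ASES score and the Constant-Murley shoulder score were obtained during the preoperative stage". The section then adds four postoperative visits, at months 3, 6, 12 and 24. Two scores and four postoperative visits appear under this heading, and none is singled out.
- **Plans to promote participant retention and complete follow-up {18b}**: "The primary outcome is set to be evaluated 3 months after the intervention". No score is named.
- **Sample size {14}**: "Sample size calculation for ASES score analysis was performed with an expected standard deviation (SD) of 5.8". The earlier SCR result behind it is described as "the score was 87.6 ± 5.8 at the latest follow-up", with no duration given. A second SCR series, 93.1 ± 8.1, is also cited. The test settings are "0.05, two-tailed) and a power of 90"%, giving 25 per group and 58 recruited.
- **Statistical methods {20a}**: each metric variable is compared between groups by a t test or Mann-Whitney U test, and a p "value less than 0.05 was considered statistically significant". No visit is named.
- **Interim analyses {21b}**: the interim takes place once half of the randomized patients have reached the primary endpoint, so its date follows from whichever definition applies.

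**The concern.** A confirmatory trial needs one identifiable comparison, or a stated rule for combining several. Here one section offers eight postoperative comparisons and another fixes a single visit that the first does not single out. A reader of the final report could not tell from the protocol whether a significant Constant-Murley difference at 6 months, say, would count as success.

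Three things depend on the answer: the false-positive rate attached to a claim of superiority, whether the stated power applies to the comparison that decides the trial, and when the interim analysis happens.

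**Working it through.** **1. Reproducing the stated sample size.** Inputs from Sample size {14}: SD 5.8, two-sided alpha 0.05, power 0.90. The target difference is not written out. I take it as 93.1 − 87.6 = 5.5, which is an inference.

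- Normal approximation: n = 2 × (1.960 + 1.282)² × (5.8/5.5)² = 2 × 10.51 × 1.112 ≈ 23.4, so 24 per group.
- Noncentral t: 24.4, so **25 per group**, with power 0.907 at 25.

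The plan's 25 reproduces. It is the figure for one score, one visit and one test.

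**2. Chance of at least one false positive with no true difference**, each test at two-sided 0.05. Under independence this is 1 − 0.95^k. The correlated figures come from simulation (400,000 multivariate normal draws per setting). The correlations are assumed, because the protocol gives none: 0.5 to 0.9 between scores and 0.3 to 0.8 between visits.

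| Reading | k | Independent | Correlated (assumed) |
|---|---|---|---|
| One score at 3 months | 1 | 5% | – |
| Two scores at 3 months | 2 | 9.75% | 7 to 9% |
| One score at four visits | 4 | 18.5% | 11 to 17% |
| Two scores at four visits | 8 | 33.7% | 16 to 30% |

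**3. Power if several comparisons stay primary and are adjusted** (Bonferroni, difference 5.5, SD 5.8):

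- Two scores at one visit, alpha 0.05/2 = 0.025: 84.7% at 25 per group; 29 per group needed for 90%.
- Eight comparisons, alpha 0.05/8 = 0.00625: 68.7% at 25 per group; 38 per group needed for 90%.

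**4. Do the sizing inputs carry over to 3 months?** Nothing in the protocol says so. The 87.6 ± 5.8 comes from an undated last follow-up, and the rehabilitation text says "Active range of motion and strengthening exercises were started approximately 3 months post surgery". To show how much depends on this, here is power at 25 per group under assumed 3-month values:

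- Difference 5.5 with SD 8.1: 65%. With SD 10: 48%.
- SD 5.8 with difference 4: 67%. With difference 3: 43%.

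These are illustrations, not estimates.

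**5. Interim date.** Trial status gives recruitment from January 2024 to January 2026. Assuming even accrual, patient 29 of 58 enters about January 2025. Adding the endpoint visit:

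- 3 months: about April 2025, with recruitment open.
- 24 months: about January 2027, a year after recruitment closes.

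**The case against.** The strongest defence reads the sections together. The Primary outcome text is worded as a collection schedule. The sample size section speaks of a single primary indicator within an ASES calculation. Section {18b} is the only sentence that dates the primary outcome, and the abstract frames the question as early efficacy. On that reading the primary is ASES at 3 months, with a 5% error rate. A rule for multiplicity is also commonly left to an analysis plan, which is not shown.

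Part of this stands. ASES at 3 months is a possible reading, and the absence of an adjustment rule would not be a finding by itself. But the reading has to be assembled from scattered sentences, and it overrides a section headed Primary outcome that names two scores and singles out no visit. An analysis plan would have to overrule one of these statements, so this is a contradiction and not omitted detail.

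Several stronger inferences are tempting and are not supported:

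- **That there are three rival endpoints.** The last follow-up in the sample size section describes where a mean and SD came from. It does not declare an endpoint time for this trial.
- **That a false positive is likely.** Even the worst case, eight independent tests, gives about 34%, and the narrower readings give 5 to 10%.
- **That the 3-month version is underpowered.** The protocol gives no 3-month difference or SD, so the version is unsupported by the sizing, not shown to fail.
- **That the start of strengthening at about 3 months invalidates a 3-month score.** That is a clinical judgement. The timing shows only that late values cannot be assumed to transfer.
- **That the sizing basis is 24 months.** The source follow-up is undated.

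**Conclusion.** The concern holds in this form: two conflicting endpoint statements, plus a sample size for one score whose inputs are tied to no visit of this trial. The 90% power is correctly computed (90.7% at 25 per group), but it belongs to a single ASES comparison that the protocol does not place in time.

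Depending on the reading, the false-positive rate runs from the nominal 5% to about 34%. For the eight-comparison reading, the range of 16 to 34% rests on assumed correlations at its lower end and on independence at its upper end. The 5.5-point difference is inferred, although it reproduces the plan's 25. The interim date can move by 21 months under even accrual.

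This needs to be settled before outcomes are compared by arm. After that, the choice of score and visit could no longer be made credibly.

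**What to change.** Before any comparison by arm:

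1. Name one primary comparison: the between-group difference in ASES, the score used for sizing, at one stated visit.
2. State the difference and SD expected at that visit, with their source, and confirm or revise 25 per group. The 24-month visit is a reasonable candidate because the inputs come from late follow-up, but the sponsor must justify whichever visit is chosen.
3. Make Constant-Murley at the same visit a key secondary, tested at 0.05 only if ASES is significant.
4. Make all other visits secondary.
5. Align Primary outcome, Sample size {14}, the retention section {18b}, Statistical methods {20a} and Interim analyses {21b} with that choice.

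**Cost.** No added visits are needed; patient numbers change only if step 2 revises the sample size. Fewer results can support a claim. Section {25} treats changes to outcome measures as substantive, so the change needs an amendment with renewed ethics approval and communication to participants, and recruitment has already begun. A 24-month primary would also put the interim after recruitment closes, where it could no longer affect enrolment. The sponsor should decide this knowingly when choosing the visit.
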